# Health coaching with physical monitoring using health wearable (HCHW) to prevent non-communicable diseases (NCDs) in the middle-aged: a 4-arm randomized controlled trial protocol

**DOI:** 10.1186/s13063-025-09081-5

**Published:** 2025-10-08

**Keywords:** Lifestyle intervention, Health coaching, Health watch, Cardiovascular disease (CVD), Non-communicable diseases (NCDs)

## Abstract

**Background:**

Non-communicable diseases (NCDs), also known as chronic diseases, contribute to a significant portion of the global disease burden and mortality. Unhealthy lifestyle factors play a major role in the development of NCDs, making middle age (35–59 years) a critical period for intervention, which can have a profound impact on delaying or preventing the incidence of chronic diseases. However, adopting lifestyle changes can be challenging, requiring interventions that consider psychological aspects and are easily incorporated into daily life.

**Methods:**

This 4-arm randomized controlled trial (RCT) aims to recruit 1000 middle-aged individuals without chronic diseases into four arms: health coaching (HC), health watch (HW), a combination of both (HC + HW), or waitlist control. The primary objectives are to assess the effectiveness of HC + HW compared to the waitlist group, as well as the effectiveness of HC-only and HW-only interventions. Secondary objectives include evaluating the impact on secondary outcomes and comparing the effectiveness between intervention groups. Life's Simple 7 (LS7) composite score will be assessed, along with biometric parameters and a risk assessment survey. Participants will undergo evaluations at 0 month, 3 months, and 6 months after randomization.

**Discussion:**

This 4-arm RCT will inform the effectiveness of HC and HW to support the community health by encouraging compliance to healthy lifestyle that prevent NCDs.

**Trial registration:**

This study was registered on Chinese Clinical Trial Registry on 26th February 2024 (no.: ChiCTR2400081193). All registered items are included within this manuscript.

**Supplementary Information:**

The online version contains supplementary material available at 10.1186/s13063-025-09081-5.

## Background

Non-communicable diseases (NCDs), commonly referred to as chronic diseases, constitute over 50% of the worldwide disease burden and cause 71% of global mortality annually [1–3]. Unhealthy lifestyles are the primary cause of NCDs, accounting for more than two-thirds of new cases [2]. Middle age, spanning 35 to 59 years, represents a critical juncture for intervention. For instance, the incidence of NCDs, including hypertension (HT) and diabetes mellitus (DM) nearly doubled among those aged 45–54 (from 15.7% to 34% for HT and 3.1% to 5.3% for DM) compared with the preceding age group of 35–44 in Hong Kong [4]. Research suggested that maintaining healthy habits at this “golden period” can have a profound impact on delaying or preventing the onset of NCDs typically manifesting after age of 60 [5, 6]. 

However, making lifestyle changes can be challenging and requires an understanding of individualized psychological factors, such as intention, motivation, expectations, reasons for change, and barriers to adopting or maintaining new habits [7]. Therefore, lifestyle interventions should be personalized to be effective. Promoting self-efficacy, self-determination, and self-responsibility is crucial for facilitating lasting behavior change [8]. Among such interventions, health coaching and health wearables hold significant promise.

Health coaching (HC) is a personalized intervention that facilitates individuals to achieve their health-related goals [9]. Health coaches assist individuals in problem solving and decision-making that foster positive changes, utilizing communication techniques including providing support, feedback and motivation, and listening [10] based on psychological theories and techniques of behavior changes, including the transtheoretical model [11], motivational interviewing (MI) [12], and cognitive behavioral therapy (CBT) [13–15].

Health coaching is widely used for patients with NCDs, significantly improving their chronic conditions, despite limited evidence from randomized controlled trials (RCTs). Nevertheless, HC has been shown to enhance adherence to healthy lifestyle choices and medication [16–19], increase physical activity [13], and improve motivation and personal satisfaction in weight loss [20]. Additionally, HC has significantly reduced systolic blood pressure (SBP) levels, improved diabetic bioindicators such as glycemic control (i.e., glycated hemoglobin (HbA1c) and fasting blood glucose (FBG)), and lowered low-density lipoprotein (LDL) level in patients with HT [21, 22], type II DM [23, 24], and hyperlipidemia [22], respectively. Notably, a recently published large-scale quasi-experimental study (*n* = 2,106,376) showed that HC can significantly improve HbA1c levels, lipid profiles, and body weight in pre-DM individuals [25].

Health wearables or health watches (HW) are some of the most popular health gadgets that typically incorporate health -tracking functions, including fitness monitoring, heart rate (HR) monitoring, oxygen saturation (SpO2) measurement, and sleep analysis. Due to their convenience, HW enable individuals to self-monitor their personal health [26]. In theory, an HW can serve as a personal monitoring tool, helping individuals understand their biological data and gain insights into their health [26]. Despite limited research, some studies have demonstrated the effectiveness of HW in helping individuals to adopt healthy behaviors. An RCT involving type 2 DM patients (*n* = 72) showed that providing activity trackers significantly increased participants’ weekly frequency of engaging in moderate to vigorous physical activity for at least 30 min on 1.5 days and increased participants’ daily step count by an average of 1255 steps per day [27]. Another RCT highlighted the broader impacts of HW on lifestyle behaviors and psychological well-being, such as self-actualization [28]. Systematic reviews have confirmed that wearable devices can significantly increase physical activity levels in individuals with chronic cardiometabolic diseases [29, 30].

While existing RCTs targeted patients with NCDs, there is a lack of HC or HW studies targeting populations at risk of developing NCDs. Additionally, despite the growing popularity of HW, there remains a lack of convincing evidence regarding their effectiveness. This study addresses these research gaps by investigating the effectiveness of HC, HW, and their combination in encouraging lifestyle changes. By combining HC with HW, the device should offer positive feedback to participants, encouraging them to adhere to the lifestyle modification advice given during health coaching [31]. This approach aims to improve both the effectiveness of and compliance with lifestyle changes. Thus, this study will provide valuable insights into designing interventions to foster healthy lifestyle, ultimately leading to NCD prevention.

## Objective and hypothesis

Participants will be randomized to one of the following arms: HC, HW, both interventions combined (HC + HW), or waitlist control. The primary objectives of this RCT is to investigate the effectiveness of each of the three intervention arms (HC + HW, HC, HW) in improving Life's Simple 7 (LS7) composite score (an integrated lifestyle score that assesses seven health metrics for cardiovascular health as defined by the American Heart Association (AHA)) [32], compared with waitlist control. Comparisons of effectiveness between the interventional arms (HC + HW, HC, HW) will be our secondary outcomes. We hypothesize that HC and HW, individually or in combination, will improve participants’ lifestyle behaviors, resulting in a higher LS7 score, when compared with waitlist control. We further hypothesize that combining HC and HW will result in superior effectiveness than either component alone.

## Trial design

This parallel, 4-arm RCT is designed as a superiority trial to assess the effectiveness of HC and HW, individually or in combination, in promoting a healthy lifestyle among middle-aged individuals without NCDs over a 6-month period. The participants will be aged 35–59 years, at risk of developing NCDs, but without any doctor-diagnosed NCDs. A total of 1000 eligible participants will be randomized equally into one of the four arms in a 1:1:1:1 ratio (*n* = 250 per group). The four arms are HC + HW, HC-only, HW-only, and control. While participants in the three intervention groups will receive their assigned interventions, the control group will not receive any intervention but will be followed up until the end of the trial. The primary assessment time point will be at 6 months after the intervention has started. The secondary assessment will occur at 3 months, during which participants will complete a shorter version of the survey.

## Method

### Study setting, recruitment, and consent

Recruitment is conducted between March 2024 and September 2024 across six study sites in Hong Kong, including four non-governmental organizations (NGOs). Participants are recruited through NGO mailing lists, social media, advertisements, and community talks. This trial is considered an extension of our ongoing cohort study which all participants receive HC + HW intervention. Therefore, the potential participant pool is considered sufficient. Informed consent is obtained from all participants prior to their inclusion in the trial. Registration is completed on the project website, where participants provide online consent. The research team is available by telephone or email to explain the consent form. A copy of the consent form is available online. After consent is obtained, the project health coach at the participant’s chosen site arranges a meeting with the participant. During this initial meeting, the health coach thoroughly explain the consent form and study procedures to ensure that participants fully understand the study and their rights. Participants are informed that they can withdraw from the study at any time.

Afterward, participants will complete a baseline assessment before randomization that evaluates their lifestyle across seven domains: physical activity, diet, sleep, stress, personal relationships, alcohol consumption, and smoking. Table 1 outlines the categorization of lifestyle domain levels. Identifying problematic lifestyle areas will guide coaching sessions and help with planning and setting health goals. All participants, regardless of their allocation, will receive a risk assessment session that reviews their lifestyle, anthropometric measurement, and blood test results in baseline. The Standard Protocol Items: Recommendations for Interventional Trials (SPIRIT) checklist was completed (see Additional file 1) and the SPIRIT figure (Fig. 1) is attached to ensure compliance with the SPIRIT reporting guidelines [33].

**Fig. 1 Fig1:**
[figure not shown]
SPIRIT figure

**Table 1 Tab1:** Baseline risk assessment criteria of seven lifestyle domains

**Domain**	**Reference**	**Domain level**		
		**Poor**	**Intermediate**	**Ideal**
Physical activity	LS7 [91]	None—sedentary	1–149 min/week moderate or intense level of physical activity	≥ 150 min/week moderate or intense level of physical activity
Diet	MD [51]	MD score ≤ 7	8 ≤ MD score ≤ 9	MD score ≥ 10
Sleep	PSQI [53, 92]	14 < Global PSQI score ≤ 21	5 < Global PSQI score ≤ 14	0 ≤ Global PSQI score ≤ 5
Anxiety	GAD-7 [61, 63]	15 ≤ GAD-7 score ≤ 21	10 ≤ GAD-7 score ≤ 14	0 ≤ GAD-7 score ≤ 9
Personal relationship	6-item De Jong Gierveld Loneliness Scale [67]	5 ≤ Loneliness score ≤ 6	2 ≤ Loneliness score ≤ 4	0 ≤ Loneliness score ≤ 1
Alcohol consumption	AUDIT-C [49, 50]	AUDIT-C score ≥ 8	5 ≤ AUDIT-C score < 8	AUDIT-C score < 5
Smoking	LS7 [91]	Current smoker	Former smoker and quit within 12 months	Never smoked, or quit more than 12 months

### Inclusion and exclusion criteria

The inclusion criteria are as follows: (1) aged between 35 and 59 and (2) at risk of NCD development defined by at least two components of the following: 1. Body mass index (BMI) ≥ 23 kg/m^2^, 2. Diet (less than 4 components of healthy diet defined by LS7, please refer to “Primary outcome” for the detail), 3. Physical activity (< 150 min of moderate or intense level of exercise per week), 4. Smoking status (current smokers or former smokers quit within 12 months), 5. Family history of HT/DM/CVD in 1 st degree relative < 60 years of age, 6. Alcohol Use Disorders Identification Test-C (AUDIT-C) score ≥ 5, and 7. Total cholesterol (TC) level (6.2 mmol/L ≤ TC < 8 mmol/L).

The exclusion criteria are as follows: (1) unable to provide consent; (2) pregnancy; (3) do not understand Cantonese; (4) measured with blood lipid level (TC ≥ 8 mmol/L; LDL ≥ 5 mmol/L; triglyceride (TG) ≥ 5 mmol/L); (5) blood pressure (BP) (SBP ≥ 135 mmHg or diastolic BP (DBP) ≥ 85 mmHg); (6) QRISK-3 ≥ 15%; (7) with doctor-diagnosed chronic diseases and require medication (including DM, HT, CVD), chronic obstructive pulmonary diseases (COPD), depression, autoimmune diseases, and cancer.

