Participants in the HC arm will receive different coaching intensity depending on their NCD risk level (please refer to Table 2 for the definition of NCD risk level). Low-risk and high-risk participants will receive 6 to 10 sessions (co-decided by the participant and the coach), and ≥ 12 sessions during the 6-month intervention period, respectively. In the first coaching session, health coaches will review the participants’ risk profiles and use a 10-point Likert scale to assess their priority, importance, readiness, and confidence to initiate lifestyle changes (higher scores indicate greater priority, importance, readiness, or confidence). The health coach will then employ various skills, adapting to specific situations, to co-design a personalized action plan with specific goals with the participants. Participants will also receive health education through the CORE program to acquire relevant knowledge to achieve these goals. The CORE program covers three topics: physical activity, diet, and mental health. Participants in the HC arm will be assigned to one of these topics, depending on their lifestyle domain risk and their preferences. Follow-up sessions will be conducted face-to-face, via phone, or through text messaging. The participant’s compliance and progress toward the established goals will be continually reviewed, and the action plan will be adjusted as needed.

**Table 2 Tab2:** NCD risk assessment criteria

Assessment metric	Low risk	High risk	Suspected to have NCDs
Health watch	Yes	Yes	Nil
Health coaching	6–10 sessions	At least 12 sessions	Nil
CORE program	Yes	Yes	Nil

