**B component**			
BP^a,c^	SBP 120–129 mmHg or DBP < 80 mmHg	SBP 130–134 mmHg or DBP 80–84 mmHg	SBP ≥ 135 or DBP ≥ 85 mmHg
FBG^a^	< 5.6 mmol/L	5.6–6.9 mmol/L	≥ 7 mmol/L
Blood lipids	–	–	TC ≥ 8 mmol/l or TG ≥ 5 mmol/l or LDL ≥ 5 mmol/l
CVD risk	–	–	QRISK3-2018 ≥ 15%
Definition	Not meeting “high-risk” criteria	At least 2 A components and 1 B component above	At least 1 B component above

^a^AHA simple 7 criteria risk factors [91]

^b^The five diet components are as follows: (1) 4.5 cups per day of fruits/vegetables, (2) servings of fish per week (3.5-oz servings), (3) 1500 mg/day of sodium, (4) 450 kcal (36 oz) per week of sweets/sugar-sweetened beverages, and (5) 3 servings per day of whole grains (1.1 g of fiber in 10 g of carbohydrate; 1-oz equivalent servings) [91]

^c^AOBP measurement [47]: Take mean BP readings with 1 min interval between readings. Use the average of this 3 readings. Measurement conditions: 1) Quiet room with comfortable temperature; 2) No smoking, caffeine, food, or exercise for 30 min before measurement; 3) Remain seated and relaxed for 3-5 min; 4) No talking by patient or staff during or between measurements. Measurement posture: 1) Sitting with back supported by chair; 2) Legs uncrossed, feet flat on floor; 3) Bare arm testing on table; mid-arm at heart level

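### The eligibility criteria, the arm descriptions and Table 2 disagree about a participant with baseline fasting glucose of 7 mmol/L or more and no medicated diagnosis

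*Protocol article*

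**What the plan says.** **Entry.** The exclusion list in Inclusion and exclusion criteria begins "The exclusion criteria are as follows: (1) unable to provide consent; (2) pregnancy; (3) do not understand Cantonese; (4) measured with blood lipid level". It sets measured limits for total cholesterol (8 mmol/L), LDL (5 mmol/L), triglycerides (5 mmol/L), blood pressure and QRISK-3; part of the list reads "SBP ≥ 135 mmHg or diastolic BP (DBP) ≥ 85 mmHg); (6) QRISK-3 ≥ 15" per cent. The only item that mentions diabetes is "7) with doctor-diagnosed chronic diseases and require medication (including DM, HT, CVD" and other named diseases. FBG appears in neither the inclusion nor the exclusion list. Trial design describes the population as "at risk of developing NCDs, but without any doctor-diagnosed NCDs".

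**Risk class.** In Table 2 the FBG row ends "5.6–6.9 mmol/L ≥ 7 mmol/L". These are two adjacent cells, the high-risk column and then the column headed "Suspected to have NCDs". The definition row for that last column is "At least 1 B component above", and FBG is one of the B components.

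**What each class receives.** The top of Table 2 has the row "Health watch Yes Yes Nil" and ends its coaching and CORE program rows with Nil as well. The Health coaching text states the number of sessions for low-risk and high-risk participants only.

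**What each arm receives.** The Intervention section assigns watch, coaching or both according to arm, and makes no exception for any risk class.

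**The concern.** For one kind of participant the article prints rules that cannot all be followed. Someone with baseline FBG of 7 mmol/L or more and no medicated diagnosis passes the entry criteria. If randomised to an active arm, this person is due that arm's intervention under the Intervention section, is listed for none under Table 2, and has no coaching intensity defined in the text. Coaches at six sites have no single rule to apply.

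The statistical stake is modest. The Statistical analysis section keeps all randomised participants in the intention-to-treat analysis. If Table 2 was followed in practice, some active-arm participants went without watch, coaching and CORE program by rule, which would pull the estimated effect towards zero. If sites resolved the conflict differently, delivery of the intervention would also vary by site for a reason the protocol does not describe.

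**Working it through.** **Step 1: match the triggers.** Each measured trigger of Table 2's third column against the exclusion list:

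| Trigger in Table 2 | In exclusion list? | Same cut-off? |
|---|---|---|
| SBP ≥ 135 or DBP ≥ 85 mmHg | Yes | Yes |
| FBG ≥ 7 mmol/L | **No** | – |
| TC ≥ 8 mmol/L | Yes | Yes |
| TG ≥ 5 mmol/L | Yes | Yes |
| LDL ≥ 5 mmol/L | Yes | Yes |
| QRISK3 ≥ 15% | Yes | Yes |

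Five of six agree exactly, and FBG is the only one absent.

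**Step 2: does another item close the gap?** Exclusion item 7 needs a doctor's diagnosis and, as worded, a need for medication. A baseline reading alone supplies neither.

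**Step 3: is FBG known before allocation?** Outcomes measurement places blood tests at baseline. Randomization and blinding says that only eligible participants with completed baseline assessments are shown for allocation. On that description the value predates randomisation.

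**Step 4: reproduce the plan's power.** Inputs from Sample size calculation: difference 0.44, SD 1.57, N = 720 (180 per arm), Bonferroni over three comparisons at 0.05.
- Standard error of a difference: 1.57 × √(2/180) = 0.1655.
- Standardised effect: 0.44 / 0.1655 = 2.659.
- One-sided critical value at 0.05/3: 2.128.
- Disjunctive power is 1 − P(all three statistics fall below 2.128), for a trivariate normal with means 2.659 and correlation 0.5. The result is 0.9005, against 0.901 stated.

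**Step 5: size of the effect if Table 2 was followed.** The documents give no share of participants with FBG of 7 mmol/L or more, so the share q is an assumption. Suppose those people received no watch, coaching or CORE program and had no effect. The mean difference then becomes 0.44 × (1 − q), and the active arms hold 3 × 250 = 750 people.

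| Assumed q | Affected of 750 | Diluted difference | Disjunctive power, 180 per arm |
|---|---|---|---|
| 0 | 0 | 0.440 | 0.901 |
| 1% | about 8 | 0.436 | 0.895 |
| 2% | 15 | 0.431 | 0.889 |
| 5% | about 38 | 0.418 | 0.871 |

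**Step 6: the same at the retention seen in the cohort.** The article reports 3.8% dropout there, and 1000 × (1 − 0.038) / 4 is about 240 per arm. At q = 5% the standardised effect is 0.418 / (1.57 × √(2/240)) = 0.418 / 0.1433 = 2.917, and disjunctive power is 0.943, above the planned 0.901.

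**The case against.** The strongest reply is that Table 2 is not an allocation rule. The text cites it for the definition of risk level, and its watch, coaching and CORE program rows do not vary by arm. Taken literally, its Yes entries would put a watch on participants in the coaching-only and waitlist arms, which the arm descriptions rule out. The table may instead describe triage in the wider programme, since the trial extends a cohort in which everyone received both interventions. This stands in part: it makes non-delivery one reading rather than a settled fact. It does not remove the conflict, because the same table also fixes coaching intensity for trial participants.

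A second reply is that FBG was simply dropped when the exclusion list was written. With five of six triggers matching, that is plausible. The printed eligibility criteria would still be wrong and need correction.

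A reader might infer more than the documents support:
- **That such people were randomised and received nothing.** No enrolment of this kind is shown, and every participant gets a risk assessment session, so at most watch, coaching and CORE program were withheld.
- **That the trial is not in its stated population.** Trial design requires only the absence of doctor-diagnosed disease, and Table 2 says suspected.
- **That these participants distort the primary outcome because the FBG item can move by 2 points.** Every LS7 item runs from 0 to 2, and current smokers and people with BMI of 25 kg/m² or more, who are recruited on purpose, have the same room to move. With randomisation and adjustment for baseline LS7, this shows no bias.

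**Conclusion.** The inconsistency is certain from the text: both rules are printed in full and give opposite instructions for the same person, so it is not a detail left to a fuller document. Whether it affected anyone is unknown. Its statistical size rests on three assumptions: a share of 1-5%, withholding of watch, coaching and CORE program from all of those people, and no effect in them. Under these, the loss in disjunctive power is at most about 0.03 (0.901 − 0.871), and it is more than offset if retention is near the cohort's. The point should be corrected because eligibility and receipt of the intervention must be unambiguous, not because the trial's power or validity is in serious doubt.

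**What to change.** 1. Reconcile Inclusion and exclusion criteria, Intervention, Health coaching and Table 2, so that eligibility and receipt of the intervention agree for FBG of 7 mmol/L or more. Which clinical rule applies is for the investigators to state.
2. Recruitment has closed, so before unblinding, list all randomised participants with baseline FBG of 7 mmol/L or more. Someone outside the blinded analysis team should record whether each was given the arm's intervention.
3. If the list is empty, say so in the report; nothing further is needed.
4. If it is not empty, keep these participants in the intention-to-treat analysis as randomised, and add one sensitivity analysis of LS7 that leaves them out in all four arms. Because the selection uses a value taken before randomisation, it preserves the randomised comparison.

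The cost is a text correction, one listing and, if needed, one extra model run. No new data are required.
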